**Fig. 1 Fig1:**
[figure not shown]
Overview of study visits

### Study population

In total, 80 GBA-PD patients will be included in this trial. In order to be included, subjects must have been diagnosed with PD according to Movement Disorders Society (MDS) criteria [46].

Patient’s should have a disease duration of under 10 years at inclusion, and they should be proven carriers of a GBA mutation. Subjects who are unable to undergo an MRI scan or have Deep Brain Stimulation (DBS) are excluded from this study. For a detailed overview of the in- and exclusion criteria, see Table 1.

**Table 1 Tab1:** In- and exclusion criteria

Inclusion criteria	Exclusion criteria
Diagnosis of PD	Refusal to be informed about an unforeseen clinical finding
Disease duration of < 10 years	Use of DBS
Proven carrier of GBA-mutation	Confirmed dysphagia
Able to write written informed consent	Known sensitivity to study medication
Able to understand protocol	MRI incompatible implants in body
Able to self-administer oral ambroxol	Pregnant or breastfeeding
	Clinically significant medical or surgical condition

#### Recruitment strategy

GBA-PD subjects are selected from a national cohort of GBA-PD patients, identified via a nation-wide screening in the Netherlands, from ongoing GBA screening of the patients of our outpatient PD expertise center and from participants with a GBA mutation of the Dutch Parkinson Cohort study (DUPARC) [47].

Finally, extra GBA-PD participants will be recruited from patients belonging to the Parkinson Platform Northern Netherlands (PPNN), which is a collaborative network of PD treating neurologists in the northern part of the Netherlands. PD patients will be asked to collect a saliva sample for full *GBA* gene sequencing. GBA-carriers will be asked to participate in the study.

### Interventions

The ambroxol capsules of 600 mg were produced exclusively for this study by a Dutch pharma company. Patients will be titrated up to ambroxol 1800 mg/day or placebo (one capsule three times a day) in 3 weeks, starting with 600 mg once daily during the first week, with weekly increases of 600 mg/day. The dosages of the individual subjects will be decreased if serious side effects occur that are probably related to the treatment.

At 48 weeks, all patients stop using either ambroxol or placebo, followed by a 12 week washout period. This washout period ensures the absence of any symptomatic effect of ambroxol.

At 60 weeks, all baseline measurements will be repeated. Participants will continue their regular medication regimen during the study. Dose adaptations of their standard regimens will be allowed, and will be analyzed post-hoc.

### Outcomes

The primary endpoint of this study is the change in the MDS-UPDRS part III motor subscale in the practically defined OFF medication state between baseline and 60 weeks. The MDS-UPDRS part III is a motor scale using a score range from 0 to 132 points, with 0 indicating no disability and 132 indicating total disability. All 18 items are evaluated on a five-point scale from 0 to 4. All items contain clearly formulated instructions for both the patient and the investigator [46, 48]. MDS-UPDRS part III in OFF medication state will be assessed every 12 weeks. OFF medication state is defined as withdrawal from dopaminergic medication for at least 8 hours. To ensure the reliability of the UPDRS III scores, several measures were implemented. First, all examiners had to pass the formal MDS-UPDRS training. All MDS-UPDRS III assessments are video recorded and scored by or together with the main co-investigator.

The study has several secondary endpoints, which are also comparing data at 60 weeks versus baseline scores. The following secondary endpoints will be assessed during this study.

*[*
^*18*^
*F]F-DOPA PET*

The PET tracer [^18^F]F-DOPA PET binds to aromatic amino acid decarboxylase (AADC) and estimates the rate of decarboxylation of [^18^F]F-DOPA to [^18^F]fluorodopamine which corresponds to striatal dopamine production and is considered a reliable tool to assess nigrostriatal dopamine synthesis capacity in vivo [49]. The PET-scan is performed after at least 6 hours of fasting (4 hours for diabetic patients). Participants are premedicated with carbidopa, 60 minutes before receiving 200 MBq of the F-DOPA tracer. The F-DOPA PET scan is performed 90 minutes after injection of the tracer on a Siemens HR+ camera. [^18^F]F-DOPA PET will be performed at baseline and at 60 weeks, to analyze the change in striatal activity. [^18^F]FDOPA striatal-to-occipital ratios of the putamen and caudate nucleus will be calculated to quantify the striatal dopaminergic innervation.

*MRI*

A structural MRI will be performed, which will also serve as the template for PET analysis. In addition, resting state f-MRI will be performed. Fluctuations in the BOLD signal will be used to investigate the functional architecture and connectivity within the brain. Variations in the nigrostriatal projections between the ambroxol and placebo groups will be analyzed using diffusion tensor imaging (DTI) MRI. The microstructural degradation of the nigrostriatal tract in PD patients is associated with the severity of motor symptoms [50]. All MRI sequences will be performed at baseline and 60 weeks.

*GCase activity and SL measurements in mononuclear cells and blood plasma*

The GBA gene encodes the lysosomal enzyme GCase, which catalyzes the hydrolysis of the SL GluCer to produce ceramide. Progression-related single allele mutations are associated with a mild (up to 50%) loss of GCase activity [51]. However, the GluCer levels of PD patients with and without GCase did not show significant differences [27, 30, 31].

So, there are still many questions to be answered about the relationship between lower GCase activity and faster disease progression [52]. Reduced GCase activity may not be related to absolute changes of SLs, but to a reduced flux (the amount of SL recycled per time) through the SL recycling pathway [33]. The recycling SL pathways are required to maintain the availability of cytosolic ceramide, which is needed to adapt and/or repair all kinds of lipid-bilayer membranes in the cell [53]. Unfortunately, measurements of the SL flux are very complex and expensive, and still need validation. Alternatively, static SL levels might give a valuable insight in the effect of ambroxol on the recycling pathway. However, recent data on the biomarker profile of SL in GBA vs non-GBA PD patients did not show any correlation between static intra- and extracellular SL levels. Moreover, only plasma measurements of SL showed differences between GBA-PD, idiopathic PD and healthy volunteers. At the same time, plasma measurements of SL showed the lowest intra-patient variability [54]. Therefore, we choose to perform only static SL measurements in plasma, including all pivotal pathways related to the formation or breakdown of ceramide.

Additionally, the effect of ambroxol on the enzymatic activity of GCase will be measured. GCase activity will be quantified in peripheral blood mononuclear cells (PBMCs), using 5-(Pentafluorobenzoylamino) Fluorescein Di-beta-D-Glucopyranoside (PFB-FDGlu) [55].

The following sphingolipids will be measured (isomers):Ceramide (d18:1/18:0)Glucosylceramide (d18:1/18:0)Galactosylceramide (d18:1/18:0)Sphingomyelin (d18:1/18:0)Dihydroceramide (d18:1/18:0)Ceramide-1-phosphate (d18:1/18:0)Sphingosine (d18:1)Sphingosine-1-phosphate (d18:1)

Figure 2 shows a schematic overview of part of the SL pathway and the specific measurements performed. Measurements will take place at baseline and after 12, 48 and 60 weeks.

**Fig. 2 Fig2:**
[figure not shown]
Schematic overview of SL metabolism

*Montreal cognitive assessment (MoCA)*

Cognitive impairment is a common non-motor symptom in PD and is an important determinant of functional outcome and quality of life. It affects approximately one in four non-demented PD patients [56, 57]. After a 10-year survival, at least 75% of PD patients will develop Parkinson’s disease dementia (PDD) [58]. The cognitive profile of PD is heterogeneous, but impaired executive functioning is the most prominent symptom [59]. The MoCA is widely used as a global assessment of cognitive function. Therefore, it will be assessed in the ON state at baseline and at 60 weeks.

*The non-motor symptoms scale (NMSS)*

The NMSS is a validated 30-item scale to quantitate various non-motor symptoms of PD. All items are rated both in severity (0–3 points, indicating “none”, “mild”, “moderate” and “severe”, respectively) and frequency (1–4 points, indicating “rarely”, “often”, “frequent” and “very frequent”, respectively) with the eventual score per item being the product of those numbers. This adds up to a final score of 0–360 points, with 0 points indicating no experience of symptoms and 360 points indicating maximum experience of symptoms. The NMSS can be used in all stages of disease progression [60]. The NMSS will be assessed in the ON state at baseline and at 60 weeks.

*Parkinson’s disease questionnaire (PDQ-39)*

The PDQ-39 is a 39-item questionnaire to assess the quality of life of PD patients and consists of 8 domains: mobility, activities of daily of living, emotional well-being, stigma, social support, cognition, communication, and bodily discomfort [61]. All items are rated based on a five-point scale (never, occasionally, sometimes, often, always), scoring 0–4 points, respectively. The total score is calculated by adding up all points scored per item. PDQ-39 will be assessed in the ON state at baseline and at 60 weeks.

*Safety*

Side-effects and other AEs will be monitored closely during the trial. For the first 3 weeks, during the titration phase, participants will receive a phone call once a week to assess possible side-effects. They will be asked to report openly first and will then be read out a selection of specific known side-effects of ambroxol to assure thorough reporting. All AEs will be followed until they have abated, or until a stable situation has been reached. Depending on the event, follow up may require additional tests or medical procedures as indicated, and/or referral to the general physician or a medical specialist.

*Other study parameters*

This study will register also the following items to characterize the study population and to monitor side effects.Demographics, including age at onset of PD, sexLEDIntoxications: alcohol and drug useIntake: six-monthly food diary entailing the last weekMedical history:General medical historyNeurological comorbidityMedical family history

#### Sample size and power calculation

The primary endpoint of this study is the difference in the MDS-UPDRS part III score between the practically defined OFF-state at baseline and 60 weeks, of the ambroxol treated group versus placebo. A previous study with 17 moderate PD patients, treated with high dosages of ambroxol, found an improvement of 6.8 (SD 7.1) points on the MDS-UPDRSIII after 186 days of treatment. However, this was in an open-label non-controlled setting [39].

Ambroxol has never been used for this indication in a double-blind placebo-controlled setting, so insufficient information is available to make a sample size calculation. The effect size was therefore based on collected data about natural disease progression of GBA-PD subjects. Enriching a clinical trial with subgroups of patients, predicted to progress faster on the primary outcome, will considerably reduce the trial size [62]. Several studies calculated the motor progression of GBA-PD. Firstly, GBA-PD patients compared to non-GBA-PD showed a 69% higher decline per year in GBA mutants [62]. Another study reported similar results, with a mean change in the MDS-UPDRS III score per year of 3.4 points (SD 7.7) in GBA carriers. Extrapolating these data to 60 weeks, we postulate an expected difference in MDS-UPDRS-III score of 3.91 points between baseline and 60 weeks in the placebo group. If we would assume no change in MDS-UPDRS III between baseline and 60 weeks in the ambroxol group, a sample size of 80 patients would be required, taking into account a two-sided 5% significance level and a common SD of 6.1, with a power of at least 80% to detect this difference in change of the MDS-UPDRS III score between patients receiving ambroxol and placebo.

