## Methods/design

### Trial design

This study is a randomized, placebo-controlled trial with ambroxol in non-demented PD patients with a proven GBA mutation. This study is reported following the SPIRIT guidelines (see Supplementary file 1) [45].

This is a single-center trial carried out in the University Medical Center Groningen, with ambroxol versus placebo during 48 weeks, followed by an open 12-week washout period, creating an overall duration of 60 weeks. During these 48 weeks, patients will receive either ambroxol 1800 mg/day or placebo. This includes a 3 week titration period, in which the dose will be increased with 600 mg/day every week. The primary endpoint is the change in off-period scores of the Unified Parkinson’s Disease Rating Scale of the Movement Disorder Society (MDS-UPDRS) part III between baseline and 60 weeks, including a 12-week wash-out period, to exclude an unlikely therapeutic effect of ambroxol. Secondary endpoints are also compared between baseline and 60 weeks, and include safety/tolerability of ambroxol, change in GCase activity in monocytes, striatal F-DOPA uptake as measured by [18]F-DOPA PET scans of the brain, resting state fMRI, related to structural MRI and diffusion tensor imaging (DTI) tractography, quality of life (QoL), measured by the Parkinson’s Disease Questionnaire-39 (PDQ-39), the presence and severity of non-motor symptoms using the Non-Motor Symptoms Scale (NMSS), cognitive changes measured by the MOCA and finally the changes in Levodopa equivalent doses (LED). For an overview of study visits, see Fig. 1.

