#### Allocation/randomization

After inclusion, baseline measurements will take place at the University Medical Center Groningen (UMCG). The study drugs (ambroxol and placebo) will be identical in appearance. The capsules will be supplied in brown glass bottles and will only be identifiable by the randomization number. Subjects will be randomized using block randomization and are stratified by sex and disease duration at time of inclusion (0–5 years and 5–10 years). Disease duration will be defined in years and months. ALEA Clinical software will be used for random assignment to placebo or ambroxol [63].

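### The stated 80% power requires progression to stay fully arrested through the 12 weeks off drug; if arrest ends with dosing, power is about 62%

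*Protocol article*

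**What the plan says.** All references are to the protocol article.

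- **Schedule.** Under Interventions: "At 48 weeks, all patients stop using either ambroxol or placebo, followed by a 12 week washout period". Under Trial design, the 48 weeks of treatment are "followed by an open 12-week washout period, creating an overall duration of 60 weeks". The primary endpoint is the change in OFF-state MDS-UPDRS part III from baseline to week 60.
- **Placebo arm.** Under Sample size and power calculation, a natural-history rate of 3.4 points a year in GBA carriers is extrapolated: "we postulate an expected difference in MDS-UPDRS-III score of 3.91 points between baseline and 60 weeks in the placebo group".
- **Ambroxol arm.** The same section continues: "If we would assume no change in MDS-UPDRS III between baseline and 60 weeks in the ambroxol group". The planned difference is therefore 3.91 − 0 = 3.91 points.
- **Result.** The total is put at 80 patients, for a two-sided test at the 5% level and an SD of 6.1 in both arms. The claim attached to it reads: "with a power of at least 80% to detect this difference in change of the MDS-UPDRS III score".
- **Purpose of the washout.** Trial design, Interventions and Discussion all justify it as a way to remove any symptomatic effect. None of them says that protection is expected to continue after drug is stopped.

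**The concern.** The planned difference credits ambroxol with 60 weeks of prevented progression, while the schedule gives 48 weeks of drug. If the drug slows the disease only while it is taken, both arms progress at the natural rate during washout, and the ambroxol arm should have worsened by about 0.8 points by week 60 even after complete arrest on treatment. The planned difference then includes 12 weeks of benefit that the treatment period does not supply.

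What is at stake is how a null result is read. A reader will set it against a stated power of at least 80%. If arrest ends with dosing, a drug that fully stopped progression for 48 weeks would be missed about 38% of the time (100% − 62%).

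**Working it through.** **Inputs from the article.** Rate 3.4 points a year; common SD 6.1; two-sided 5%; 80 patients; 48 weeks on drug; endpoint at week 60. **Assumed:** 1:1 allocation, so 40 per arm. No ratio is printed, but this one reproduces the stated size.

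**Step 1: the planned difference.** With 365.25/7 = 52.18 weeks a year, 3.4 × 60/52.18 = 3.91. It reproduces.

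**Step 2: the stated power.** Two-sample t-test, n = 40 per arm:

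- standard error = 6.1 × √(2/40) = 1.364
- noncentrality = 3.91/1.364 = 2.87 on 78 degrees of freedom
- power = 80.8% (81.8% by the normal approximation)

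With 39 per arm the t-test gives 79.8%, so 40 per arm is the smallest size that reaches 80%. The stated 80 patients reproduce, with less than one percentage point to spare.

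**Step 3: arrest on drug only.** Assume linear progression (the article's own extrapolation) and immediate return to the natural rate at week 48 (not stated in the article).

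- difference = 3.4 × 48/52.18 = 3.13 (equally, 3.91 × 48/60)
- washout progression no longer prevented = 3.91 × 12/60 = 0.78
- noncentrality = 3.13/1.364 = 2.29
- power = 62.0% (63.1% by the normal approximation)

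For scale, 80% power at 3.13 points would take 61 per arm, or 122 in total.

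**Step 4: partial persistence.** Let f be the share of washout progression that is still prevented. The difference is 3.91 × (48 + 12f)/60.

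| f | Difference (points) | Power (t-test, SD 6.1) |
|---|---|---|
| 0 | 3.13 | 62% |
| 25% | 3.32 | 67% |
| 50% | 3.52 | 72% |
| 75% | 3.71 | 77% |
| 100% (the plan) | 3.91 | 81% |

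**Step 5: how much persistence 80% needs.** The difference detectable with 80% power at 40 per arm and SD 6.1 is 3.87 points. Setting 3.91 × (48 + 12f)/60 = 3.87 gives 48 + 12f = 59.39, so f = 0.95. Essentially all of the arrest has to survive the 12 weeks off drug.

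**Step 6: the planned ANCOVA.** The primary analysis adjusts for baseline, which may help. The article gives neither a baseline correlation nor the basis of the 6.1. If 6.1 is the SD of an unadjusted change score, and variances are equal at both visits, the ANCOVA SD is 6.1 × √((1 + ρ)/2), where ρ is the correlation between baseline and week 60.

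- ρ = 0.8 (assumed): SD 5.79, power about 67% at 3.13 points
- ρ = 0.7 (assumed): SD 5.62, power about 69%
- 80% power needs SD 4.93, so ρ = 2 × (4.93/6.1)² − 1 = 0.31

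If 6.1 already reflects adjustment, there is no gain.

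**The case against.** **This is a planning assumption, not a miscalculation.** That stands. Every printed figure reproduces, and a reader who inferred an arithmetic error would be wrong.

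**The assumption is printed.** It is, conditionally and with week 60 named. The section also concedes that too little is known for a proper calculation, and the Discussion allows that expectations may prove too optimistic. What is missing is any recognition that week 60 lies 12 weeks beyond the last dose, a reason to expect arrest to last that long, and the power if it does not.

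**3.1 points is not a ceiling.** A reader might infer that even a perfect drug could not exceed 3.1 points, or that power is 62% outright. The article supports neither. Both require progression to resume its full natural rate as soon as drug stops, which no section states. A lasting, non-symptomatic gain of about 0.8 points by week 48 would also give zero change at week 60. However, the plan is built on no change, not improvement: the section describes the 6.8-point improvement in the earlier study as open-label and uncontrolled, and turns to natural progression for the effect size.

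**ANCOVA raises power.** Probably somewhat, as Step 6 shows. At the correlations tried it does not restore 80%, and no correlation is given from which to claim more.

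**Conclusion.** The point holds in conditional form. The stated power of at least 80% is correct only if complete arrest of progression persists essentially in full (about 95% or more) through 12 weeks off drug, and the article does not justify that. Without carry-over the difference is about 3.1 points and power about 62%; across the range from none to full carry-over, power runs from 62% to 81%.

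These figures rest on linear progression, 1:1 allocation, the stated SD of 6.1 and an unadjusted t-test. The 62% rests in addition on immediate return to the natural rate when drug stops. Whether 6.1 is itself a suitable SD is a separate question and plays no part here.

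**What to change.** Keep the sample size at 80 and change the text of the sample size section in one of two ways:

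- base the planned difference on 48 weeks of prevented progression, and give about 3.1 points with power of about 62%; or
- keep 3.91 points, state that arrest is assumed to persist through the washout, and print beside it the power without that assumption (62% with no carry-over, rising to 81% with full carry-over).

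In either case, add one sentence saying that the difference detectable with 80% power is about 3.87 points and that a null result will be interpreted against it. If the sponsor has a baseline correlation and knows the basis of the 6.1, the ANCOVA power can be given instead of the t-test figure.

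The cost is one restated figure and one or two sentences. Schedule, endpoint and analysis are untouched. The downside is that the stated power becomes less favourable.

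### The claim of at least 80% power rests on an SD of 6.1 that is below both SDs the section quotes and is not reconciled with either; at the SD quoted with the effect size, power is about 61% unadjusted

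*Protocol article*

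**What the plan says.** All the inputs are in the protocol article, under Sample size and power calculation. Two SDs for MDS-UPDRS III change are quoted there. The open-label ambroxol study of 17 patients "found an improvement of 6.8 (SD 7.1) points on the MDS-UPDRSIII after 186 days of treatment". A natural-history study reported similar results to a preceding one, "with a mean change in the MDS-UPDRS III score per year of 3.4 points (SD 7.7) in GBA carriers".

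The effect size is built on the second of these: "we postulate an expected difference in MDS-UPDRS-III score of 3.91 points between baseline and 60 weeks in the placebo group". The ambroxol arm is set to zero progression: "If we would assume no change in MDS-UPDRS III between baseline and 60 weeks in the ambroxol group". The design difference is therefore 3.91 points.

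The calculation then concludes that 80 patients are required, "taking into account a two-sided 5% significance level and a common SD of 6.1, with a power of at least 80" per cent. Study population gives the same figure, 80, as the number to be included. Statistical analyses specifies an ANCOVA adjusted for baseline score and stratification factors. It includes patients with at least one post-randomization follow-up visit. Missing data specifies last observation carried forward.

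**The concern.** The mean and the SD of 7.7 stand in the same sentence, from the same study. The mean was kept and scaled up to 60 weeks, while the SD was replaced by a smaller one. The published text gives no reason, and the only other SD it quotes is also larger than 6.1. The power claim therefore holds only at a value that nothing else in the section supports.

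What is at stake is how the primary result is read. The design difference already assumes that ambroxol stops progression completely over 60 weeks. If true power for that full effect is nearer 60–70% than 80%, a non-significant result is weaker evidence against disease modification than the published figure suggests.

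**Working it through.** **Inputs.** Difference d = 3.91 (3.4 × 1.15, where 60 weeks is about 1.15 years); two-sided 5%; 80 patients; SDs 6.1 (used), 7.1 and 7.7 (quoted). The allocation ratio is not stated, so 1:1 is assumed, giving n = 40 per arm.

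**Method.** Two-sample t-test on change, power from the noncentral t with 78 degrees of freedom. SE = SD × √(2/n) = SD × √0.05; noncentrality = d/SE; two-sided critical value t = 1.991.

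**The plan's own figure.** SE = 6.1 × 0.2236 = 1.364; noncentrality = 3.91/1.364 = 2.87; power = 80.8%. The smallest n per arm reaching 80% is 40, which is 80 in total. The normal approximation gives 39 per arm, 78 in total. The stated sample size is reproduced.

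**The same calculation at the quoted SDs.**

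| SD | SE | Noncentrality | Power with 80 | Total N for 80% | Difference detectable with 80% power |
|---|---|---|---|---|---|
| 6.1 | 1.364 | 2.87 | 80.8% | 80 | 3.87 |
| 7.1 | 1.588 | 2.46 | 68.2% | 106 | 4.50 |
| 7.7 | 1.722 | 2.27 | 61.1% | 124 | 4.88 |

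The largest SD at which 80 patients still give 80% power is 6.16. Both quoted SDs exceed it.

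**Allowing for the planned ANCOVA.** Suppose the quoted SD is that of the raw change, the variances at baseline and week 60 are equal, and the two scores correlate at ρ. The variance of change is then 2σ²(1 − ρ) and the ANCOVA residual variance is σ²(1 − ρ²). Hence residual SD = SD of change × √((1 + ρ)/2). The documents give no ρ; 0.6–0.8 is an assumed range.

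- SD 7.7, ρ = 0.6: 7.7 × √0.8 = 6.89; power about 71%.
- SD 7.7, ρ = 0.8: 7.7 × √0.9 = 7.30; power about 66%.
- SD 7.1, ρ = 0.6 and 0.8: 6.35 and 6.74; power about 78% and 73%.

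**What would turn 7.7 into 6.1.** Set √((1 + ρ)/2) = 6.1/7.7. Then ρ = 2 × (6.1/7.7)² − 1 = 0.26. Put another way, baseline would have to explain 1 − (6.1/7.7)² = 37% of the variance of change. In this model a higher ρ makes adjustment less helpful relative to the change score. So 6.1 is reached only if baseline and week-60 motor scores are weakly correlated.

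**Margin.** At SD 6.1, 39 per arm gives 79.8% by the t-test. The number to be included equals the number required, so the t-test calculation has no reserve.

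**The case against.** Several points on the other side stand.

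- *There is no calculation error.* A reader might infer that the sample size was computed wrongly. It was not: 80 follows from 6.1. The point concerns an input only.
- *61% is not the power of the planned test.* It belongs to an unadjusted comparison of change, and the protocol plans ANCOVA. At SD 7.7 adjustment raises it to about 66–71% under the assumptions above, which does not reach 80%.
- *The 7.1 is weak evidence.* It comes from 17 patients over 186 days. Assuming normality, its 95% interval is about 5.3 to 10.8, which includes 6.1. So 7.1 does not exclude 6.1, but it is not a source for it. With adjustment, 7.1 comes close to 80%. The main discrepancy is with 7.7, which belongs to the effect size.
- *What 7.7 measures cannot be checked.* It could be the SD of a one-year change or of annualised rates over varying follow-up. Whether it should grow when taken to 60 weeks is therefore open, and no scaling is applied here.
- *A journal article condenses.* The origin of 6.1 may be in the full protocol, and the lack of a citation alone would not be a finding. But the article printed 7.7 beside the mean it used and then planned on 6.1, so the mismatch is in the published text.
- *Drop-out.* A reader might take an assumed 10–15% loss at week 60 and recompute power with 36 or 34 per arm. The documents do not support that. Motor scores are taken every 12 weeks, patients with one follow-up visit stay in, and missing values are carried forward, so most drop-outs remain in the headcount. Carrying early scores forward would be expected to dilute a difference that builds over time, but nothing in the documents allows that to be quantified.

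**Conclusion.** The point holds as an unsupported input to the power statement. At the SD quoted with the effect size, 80 patients give about 61% power unadjusted, or about 66–71% under ANCOVA with an assumed correlation of 0.6–0.8 and equal variances. At SD 7.1 the unadjusted figure is about 68%. Power of 80% is available only at an SD of about 6.16 or less. All figures assume 1:1 allocation and a true difference of 3.91.

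The stronger conclusion, that the trial is known to have 61% power, does not follow: 6.1 may be justified as a residual SD or from a source not shown. What follows is that the published text gives no basis for preferring 6.1 to the SD printed beside its own effect size.

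The consequence is one of interpretation. The 95% half-width (1.991 × SE, unadjusted) is 2.7 points at SD 6.1 and 3.4 at SD 7.7. An observed benefit of 1 point would then have an upper limit of 3.7 in the first case, excluding the full 3.91, and 4.4 in the second, not excluding it. The endpoint, the analysis and the type I error rate are unaffected. This should be fixed, but it does not threaten the trial's validity.

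**What to change.** Reconcile 6.1 with 7.7 in the sample size section. If 6.1 is an ANCOVA residual SD, say so and state the correlation used. If it comes from another source, name the source and explain why its SD is preferred to the one accompanying the effect size.

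Otherwise restate power as a range, for example: *For a difference of 3.91 points, 80 patients (40 per arm) give about 81% power at SD 6.1, 68% at SD 7.1 and 61% at SD 7.7, unadjusted; at SD 7.7 with baseline adjustment, about 66–71% assuming a baseline/week-60 correlation of 0.6–0.8. The differences detectable with 80% power, unadjusted, are 3.9, 4.5 and 4.9 points.* Add that the number to be included equals the number required, so there is no reserve.

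Commit to interpreting a non-significant primary result by its confidence interval, with reference to whether 3.91 points is excluded.

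The cost is a less favourable published figure. No extra enrolment and no change to the design or the analysis is needed.
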